#### Procedures

Participants at both sites will receive PMTCT services guided by the Kenyan national guidelines [7]. At the time of PMTCT enrollment (first visit), all eligible women will be informed about the study by the clinical staff, and written informed consent for participation, including a review of hospital records documenting PMTCT services, will be obtained by a trained hospital staff member.

##### Training of Hospital and Study Staff

Key hospital personnel (PMTCT and maternity nurses and mentor mothers) will be trained by employing hands-on data entry scenarios tailored to the specific capacity in which they will utilize the HITSystem 2.0. During the first weeks of implementation, the trained research assistant (RA) will work closely to ensure thorough understanding and accurate independent use of the HITSystem 2.0 and will be available throughout the study to retrain or assist in system-related problem solving. The RA will be based in the MCH department with PMTCT providers to monitor and support fidelity to intervention implementation and timely data entry into the HITSystem 2.0. The US-based HITSystem team will remotely review the entered data to identify any challenges or systematic errors to be addressed. This is the same training and implementation process successfully employed for the HITSystem pilot [33] and cluster randomized trial to evaluate EID outcomes [32]. Training at the control site will be limited to assessing participant eligibility, conducting informed consent, and administering the baseline survey. Nurses and mentor mothers directly involved in PMTCT service provision will conduct these research tasks. All research and clinical staff involved in the study will be trained on procedures to ensure participant confidentiality and secure data storage.

*Baseline surveys* will be conducted at the initial PMTCT enrollment visit at both intervention and control sites for all eligible women. In addition to the basic demographic information captured in routine care at both hospitals (age and number of children), questions will assess (1) knowledge and perceived importance of attendance at scheduled appointments; ART before, during, and after delivery; consequences of poor adherence; and infant testing, (2) motivation and self-efficacy to complete the targeted behaviors (eg, attendance, medication adherence, plan for delivery, and prompt EID enrollment) using scaled and Likert responses, (3) assessment of depression symptoms (6 questions to assess frequency of symptoms between 0 to 7 days a week) and risk for intimate partner violence (3 screening questions to facilitate counseling referral), and (4) male partner involvement. Study staff will enter completed paper surveys in Excel 2016 (version 1708).

*PMTCT service utilization* will be documented in the patient file and relevant PMTCT-related facility registers (intervention and control) as required by the Kenyan Ministry of Health. At the intervention hospital, a new record will be created in the HITSystem 2.0 during PMTCT enrollment and will be updated at each subsequent visit, including mobile phone number(s) and residence tracing information. Prospective clinical data from the mother-infant pair will be captured in the HITSystem 2.0 to track medication adherence, appointment attendance, delivery outcomes, and postpartum infant prophylaxis data, automating provider alerts and SMS text messages to participants as indicated. Any information that is not captured in the HITSystem at the time of the patient’s visit (owing to workflow, connectivity, or other challenges) will be updated as soon as possible after the visit, referencing any relevant paper-based patient and facility records needed. All relevant data to measure the targeted PMTCT outcomes will be entered and maintained in the HITSystem 2.0.

At the control site, paper-based patient files and facility registries are the primary record-keeping source for PMTCT data. A study staff member will visit the control site quarterly to review clinical records to document and update PMTCT services received by women enrolled in the study. Multiple sources will be cross-referenced to collect standard of care data at the control hospital: (1) pregnant women/mothers’ medical records, (2) hospital ANC registry book, (3) pharmacy ART registry, (4) maternity registry, and (5) HIV-exposed infant registry.

*HITSystem 2.0 user satisfaction* will be assessed with semistructured interviews to solicit feedback on usefulness and acceptability of the content and frequency of the targeted SMS text messages, patient tracing efforts, and other recommendations to improve the intervention. Participants (n=35) will be purposively selected to include variation among women with complete/incomplete retention, low/high ART adherence, and facility/home deliveries. Interviews will be conducted in the language they prefer (Swahili or English) once study participation is complete. We will also conduct interviews with providers and hospital administrators to better understand the strengths and limitations of the HITSystem 2.0 implementation, its integration with the current HITSystem 1.0*,* and suggestions for improvement. Remuneration for interview participation and the analysis plan for qualitative data will be the same as described in Phase 1. Interviews will not be conducted at the control site as they did not experience the intervention.

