#### HIV Infant Tracking System 2.0 Intervention Specifications

Clear reporting of intervention components and implementation strategies is needed for meaningful application in practice or testing in research [40,41]. The entry point into the HITSystem 2.0 will be the first PMTCT appointment for women previously diagnosed with HIV or newly confirmed HIV positive during antenatal HIV screening. Actions include automated prompts to PMTCT providers, prompts to central laboratory technicians who process viral load (VL) samples, and SMS texts to patients driven by national algorithms for optimal PMTCT care (Table 1). Automated electronic prompts to providers will persist as Web-based dashboard alerts until addressed. Automated SMS texts are sent to HIV-positive pregnant women as cues to action; women can select the preferred content and frequency for one-way ART adherence text messages at the time of enrollment. This is one of the first interventions to target adherence support messages during pregnancy, thus texting options (content and frequency) will be informed by Phase 1 formative research, and actual preferences will be assessed by this pilot study. Community health care workers can reach out to patients who miss services and/or do not respond to SMS text messages or calls to encourage retention. The HITSystem 2.0 will integrate PMTCT and EID services through 1 coordinated system-level intervention; this will permit longitudinal follow-up of mother-infant pairs to assess PMTCT outcomes.

**Table 1 table1:** HITSystem 2.0 intervention components. Expected timing, dose, and target of alerts and SMS (short message service) texts to providers and HIV positive pregnant women.

Actors	Actions	Timing	Dose^a^	Target
Hospital-based providers; providers	Algorithm-driven electronic alerts	When PMTCT^b^ service late/missing (enrollment-infant EID^c^ link)	Avg=8 per mom, range=0 to 14+	PMTCT quality: complete PMTCT retention (pregnancy to EID link)
Lab-based providers; lab techs	Algorithm-driven electronic alerts	When receipt of VL^d^ sample or VL results delayed	Avg=1 per mom, range=0-2+	PMTCT efficiency: reduced turn-around time for key PMTCT services

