### Primary Outcome: Complete Prevention of Mother-to-Child Transmission of HIV Retention

The primary outcome is complete PMTCT retention, measured from the first PMTCT appointment until the infant’s first HIV test, which is targeted at 6 weeks of age. The aggregate measure of complete retention—calculated as retention before delivery, at delivery, and after delivery—will be dichotomously coded as complete or incomplete retention. Complete retention is defined as maternal ART initiated (if not already on ART at the time of pregnancy), all scheduled PMTCT appointments attended, hospital-based delivery, and HIV DNA PCR testing by 6 weeks (<7 weeks) postnatal.

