## Discussion

Previous HITSystem pilot data and studies have demonstrated significant success in improvement of EID outcomes particularly in improving the efficiency and quality of key EID outcomes [32-34,38]. Leveraging the improved linkage of health facilities, mother-infant pairs, and laboratories in the context of EID, the HITSystem 2.0 (PMTCT) will expand the current Web-based platform to bridge the gap between maternal and pediatric HIV services. Outcomes at each step of the PMTCT cascade will be analyzed, and specific challenges will be identified.

This study will design and implement the HITSystem 2.0 through formative qualitative research, intervention development using the 4Ds process, and a pilot implementation period as described above. It will also provide user satisfaction data by highlighting the HITSystem 2.0’s usefulness, acceptability, challenges, and recommendations to improve the intervention. The proposed HITSystem 2.0 will integrate maternal and infant HIV services in one system-level, Web-based intervention that will provide linked, prospective data for mother-infant pairs, which has been identified as a problematic gap in the current system. The findings of this study will refine the HITSystem 2.0 intervention, particularly tracking and utilization of challenging measures such as medication adherence and antenatal VL results to enhance system performance and implementation strategies in a larger scale efficacy trial.

Although this intervention will focus on health system improvement to enhance quality of care for women and infants in the facility setting, the study will not directly target PMTCT uptake, which would require community-based outreach. Given that intervention site data will be tracked via the HITSystem whereas control site data will be captured via disparate paper-based registries and patient files, there may be discrepancies in data quality and documentation of services rendered between control and intervention sites; all efforts will be made to capture any available data at control sites to minimize this limitation. As the study design and implementation evolve, we anticipate that eHealth technologies in the study regions will likewise evolve and influence the standard of PMTCT care. These external factors will be documented and accounted for in the design and analyses.

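### The primary outcome is captured through the intervention's own data system at one hospital and through quarterly paper abstraction at the other, so unequal documentation alone could create a difference in complete retention

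*Protocol article*

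**What the plan says.** The protocol article (Primary Outcome) codes retention as complete or incomplete. Completeness requires maternal ART initiation where not already on ART, together with "all scheduled PMTCT appointments attended, hospital-based delivery, and HIV DNA PCR testing by 6 weeks (<7 weeks) postnatal".

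The sources for these components differ by hospital (text on PMTCT service utilization, under Training of Hospital and Study Staff):

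- **Intervention.** "All relevant data to measure the targeted PMTCT outcomes will be entered and maintained in the HITSystem 2.0". Items not entered at the visit are added later with reference to paper records. In addition, "The RA will be based in the MCH department with PMTCT providers to monitor and support fidelity to intervention implementation and timely data entry", and a US-based team reviews entries remotely. Under Intervention Specifications, "Automated electronic prompts to providers will persist as Web-based dashboard alerts until addressed". Fidelity Assurance Procedures adds a routine completeness review of HITSystem entries.
- **Control.** "At the control site, paper-based patient files and facility registries are the primary record-keeping source for PMTCT data". These records reach the study dataset through a quarterly abstraction visit by study staff, who check five sources against one another: medical records, the ANC registry, the pharmacy ART registry, the maternity registry and the HIV-exposed infant registry.

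A common source exists, because service use "will be documented in the patient file and relevant PMTCT-related facility registers (intervention and control) as required by the Kenyan Ministry of Health". The Discussion concedes that "there may be discrepancies in data quality and documentation of services rendered between control and intervention sites" and undertakes to capture whatever data are available at control.

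**The concern.** The intervention is also the instrument that records the primary outcome in its own arm. That arm has electronic plus paper capture, with prompts and people to close gaps. The control arm has only what was written on paper and can be found at a quarterly visit.

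An all-or-none outcome magnifies small gaps. If a delivered service that leaves no record is counted as not delivered, one lost item turns a complete woman into an incomplete one. A difference in record-keeping could then pass for a difference in care, and the primary chi-square test cannot tell them apart.

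The plan already acts on this kind of problem elsewhere. In Statistical Analyses it gives up the between-site comparison of medication adherence because control documentation is not comparable. It keeps the between-site comparison for retention without a common source.

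**Working it through.** **1. The plan's own figure.** Power and Sample Size gives 47% versus 20%, two-sided alpha 0.05, 80% power and 54 per hospital.

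- Uncorrected: n = [1.960·√(2·0.335·0.665) + 0.8416·√(0.47·0.53 + 0.20·0.80)]² / 0.27² = 46.8, so 47 per hospital.
- With continuity correction: (46.8/4)·[1 + √(1 + 4/(46.8·0.27))]² = 53.9, so 54 per hospital.
- Reading 0.27 as Cohen's w also gives the stated total: (1.960 + 0.8416)² / 0.27² = 107.7, so 108.

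The stated sample size is reproduced and is not in question here.

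**2. Model for documentation loss.** These are assumptions, as the documents give no documentation rates.

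- Six items per woman: four visits, delivery and PCR. ART initiation would be a seventh for women not already on ART.
- Each delivered item is missing from the final control record with probability q, after cross-referencing, independently of the others.
- An unrecorded item is coded as not done.
- True retention p is the same at both hospitals, so there is no real effect.
- The intervention hospital is first taken as fully documented.

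A truly complete control woman is then coded complete with probability (1 − q)⁶:

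- 2% loss: 0.98⁶ = 0.886
- 5% loss: 0.95⁶ = 0.735
- 10% loss: 0.90⁶ = 0.531

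Observed control retention is p·(1 − q)⁶. The chance of significance comes from summing the two binomial distributions (n = 54 each) over all tables in which the uncorrected two-sided chi-square exceeds its 5% limit.

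| True p, both hospitals | Control loss per item | Observed, intervention vs control | Chance of p < 0.05 |
|---|---|---|---|
| 20% | 0% | 20% vs 20% | 5% |
| 20% | 2% | 20% vs 17.7% | 6% |
| 20% | 5% | 20% vs 14.7% | 11% |
| 20% | 10% | 20% vs 10.6% | 27% |
| 30% | 5% | 30% vs 22.1% | 15% |
| 30% | 10% | 30% vs 15.9% | 42% |
| 47% | 0% | 47% vs 47% | 4% |
| 47% | 2% | 47% vs 41.6% | 8% |
| 47% | 5% | 47% vs 34.5% | 26% |
| 47% | 10% | 47% vs 25.0% | 68% |

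The 20% and 47% are the protocol's planning rates. The 30% is an assumed intermediate value.

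**3. Sensitivity to the assumptions.**

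- *Intervention hospital also loses 2% per item.* At true 20%, the observed rates are 17.7% vs 14.7% (5% control loss) and 17.7% vs 10.6% (10%). The chances fall to 7% and 18%. At true 47% they fall to 12% and 46%.
- *Gaps fully clustered.* If all missing items fall in the same 10% of women, control reads 0.9·p, that is 18% or 42.3%. The chance is then only 6% to 7%.
- *Seven items.* At 5% loss the range is 13% to 32%. At 10% it is 33% to 78%.
- *Loss that would mimic the planned effect.* (0.20/0.47)^(1/6) = 0.867, so about 13% loss per item at control only would produce 47% versus 20% with no effect on care.

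**The case against.** Several points count against a stronger reading.

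- **The control site is not neglected.** A reader might infer that the plan offers nothing beyond good intentions. In fact it names five sources to be cross-referenced and standard operating procedures for data collection. It also provides for contacting women who deliver elsewhere to record place of birth, without limiting this to one hospital. These steps reduce the loss. They cannot recover a service that nobody wrote down.
- **Coding undocumented as incomplete is an inference.** The article gives no rule for missing documentation, and such a rule may sit in a fuller document. The inference follows from a binary definition with no third category. The difference in source, however, is stated outright.
- **The direction is not settled.** A reader might infer that bias must favour the intervention. The outcome depends on *scheduled* visits, so a missed visit must also be visible. HITSystem 2.0 flags late and missing services, whereas a paper record may never show a visit that was scheduled and missed, which would flatter the control hospital. The argument for bias towards benefit is strongest for delivery and PCR.
- **The loss rates are unsupported.** At 2% loss, or with clustered gaps, the test stays near its nominal level.
- **This is a two-hospital pilot.** With one hospital per arm, a difference cannot be ascribed to the intervention alone even with identical records. The limitation is disclosed and a larger efficacy trial is foreseen. This argues against treating the point as fatal.

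What stands is that the article specifies different instruments by arm for an outcome sensitive to small gaps, although a common source is available.

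**Conclusion.** The point holds as a risk of bias built into data capture, not as a demonstrated bias of known size or certain direction. With no true effect, six independent items and full intervention documentation, the chance of a significant result is about 6% to 8% at 2% control loss per item, 11% to 26% at 5% and 27% to 68% at 10%, over true retention of 20% to 47%. It is lower if the intervention hospital also loses entries or if gaps cluster within women. With equal documentation it is 4% to 5%.

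The planned comparison with the preceding 18 months does not clearly rescue the analysis. HITSystem 2.0 is only built within this study, so at the intervention hospital the source would change together with the intervention.

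This should be fixed. A reader might infer that the primary result is uninterpretable without the change. The documents do not support that, because the limitation is disclosed and partly mitigated, its size is unknown, and the study is a pilot.

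**What to change.** 1. Abstract the same patient files and registers at both hospitals, quarterly and on the same form. The study staff who abstract at control should do this, not the research assistant who supports the intervention.
2. Derive the primary comparison from this common source. Report the HITSystem-augmented outcome as a sensitivity analysis.
3. Apply one stated rule for undocumented services in both arms.
4. Keep the outcome's own definition based on scheduled visits, and determine the schedule in the same way at both hospitals. Replacing it with a guideline visit count would alter the endpoint and is not needed here.
5. State the remaining limitation: alerts and on-site support may improve paper charting at the intervention hospital, and a common paper source does not remove that.

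The cost is about 54 more files on a schedule that already exists for control. Services recorded only electronically would leave the primary analysis, which works against the intervention hospital and is why the sensitivity analysis is needed. The consent described under Procedures already covers review of hospital records. Results reports that no between-group outcome analysis has been done, so the rule can still be fixed without knowledge of the outcome. The common source also matches what is available for the retrospective period.

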##### Fidelity Assurance Procedures

Standard operating procedures were developed for each step of the study process to standardize training, enrollment, and all data collection procedures. As it is Web-based, any modification or corrections to the HITSystem are instantly applied across all users. HITSystem entries are routinely reviewed to ensure completeness and appropriate utilization of the comments section. Study personnel will make quarterly visits to the control site to cross-reference enrollment records with patient files and the relevant PMTCT-related facility registers and to review informed consent documents and surveys for accuracy, completeness, and secure storage.

### Primary Outcome: Complete Prevention of Mother-to-Child Transmission of HIV Retention

The primary outcome is complete PMTCT retention, measured from the first PMTCT appointment until the infant’s first HIV test, which is targeted at 6 weeks of age. The aggregate measure of complete retention—calculated as retention before delivery, at delivery, and after delivery—will be dichotomously coded as complete or incomplete retention. Complete retention is defined as maternal ART initiated (if not already on ART at the time of pregnancy), all scheduled PMTCT appointments attended, hospital-based delivery, and HIV DNA PCR testing by 6 weeks (<7 weeks) postnatal.

### Secondary Outcomes

#### Duration of Prevention of Mother-to-Child Transmission of HIV Retention

We will estimate the duration (number of weeks) of PMTCT retention for each participant by subtracting the last date of documented service engagement from the date of enrollment. This will allow comparisons between total time retained in PMTCT services between groups and identify when (antenatal, delivery, or early postnatal) disengagement from PMTCT most often occurs.

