#### Prevention of Mother-to-Child Transmission of HIV Appointment Attendance

We will measure the proportion of mothers who attended all scheduled ANC appointments, documenting late (>7 days past scheduled date) and missing (>14 days past scheduled date) attendance. The number of possible appointments will vary on gestational age at PMTCT enrollment; thus we will measure the median number of visits, the proportion who received the recommended 4 or more appointments, and the proportion enrolled by the recommended 14 weeks gestation.

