#### Statistical Analyses

To examine the baseline participant and facility characteristics, we will calculate descriptive statistics including proportions for categorical variables and means (SD) or median (interquartile range) for continuous variables [47]. For the primary outcome, chi-square tests will be used to compare the proportion with complete PMTCT retention between groups [48]. We will explore correlations between complete PMTCT retention and possible predictors (eg, knowledge, motivation to complete care, maternal HIV disclosure, perceived benefit of ART, maternal depression, and risk of intimate partner violence) using Phi, point-biserial, or Spearman rho statistics depending on the measurement level of each predictor [49]. Analytic models will control for significantly different preintervention covariates across conditions and hospitals, clustered observations (eg, time nested within setting), and gestational age as it impacts the eligible/recommended number of appointments or services.

For secondary analyses, Kaplan-Meier curves will illustrate differences in the duration of PMTCT retention before, during, and after delivery, accounting for the woman’s eligible period of engagement (based on the timing of enrollment and accounting for premature infant or maternal mortality). We will then identify time periods when meaningful decreases in PMTCT retention occur, using Cox proportional-hazard regression for survival analyses (ie, retention), if all assumptions are met [50]. Known variables associated with HIV service retention (age, disclosure status, educational level, and number of children [22,51,52]) and those correlated (*P*<.10) will then be included in a generalized linear mixed model to identify a parsimonious list of predictors.

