Using chi-square tests, we will compare the proportion of pregnant women (1) attending all scheduled PMTCT appointments (4 or more PMTCT visits and late or missed visits), (2) tested for VL (VL sample collected, results returned, and detectible VL values), (3) delivery at the hospital, (4) enrolling in EID (dried blood spot sample collected by <7 weeks), and (5) have an infant diagnosed with HIV, between intervention and control sites. The median number of PMTCT appointments, median gestational week at first PMTCT appointment, and median TAT for VL results will be calculated and compared using Mann Whitney *U* tests. Although medication adherence documentation at the control site (typically described as poor, fair, or good) will not permit direct comparison, the proportion of pregnant women at the intervention site with >95% adherence will be described. Participant preferences for the content and frequency of SMS text messages for medication adherence support will also be described. *P* values will be adjusted (using Tukey correction) for multiple tests, where appropriate. Quantitative data will be analyzed using Statistical Application Software (SAS) version 9.4.

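### Visit counts are compared between the two hospitals without allowing for gestational age at entry, and entry timing itself is listed or tested among the outcomes

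*Protocol article*

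**What the plan says.** All references are to the protocol article.

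- **Appointment Attendance (Secondary Outcomes).** The article states that "The number of possible appointments will vary on gestational age at PMTCT enrollment". From this it derives three measures: median visits, the share reaching 4 or more, and the share entering care by 14 weeks. It also keeps a measure tied to each woman's own schedule, namely whether she attended every appointment set for her.
- **Statistical Analyses.** "The median number of PMTCT appointments, median gestational week at first PMTCT appointment, and median TAT for VL results will be calculated and compared" by Mann-Whitney U. Four or more visits is placed under the chi-square comparisons between sites. Earlier in the same section, models are to control for "gestational age as it impacts the eligible/recommended number of appointments or services".
- **Intervention Specifications and Discussion.** "The entry point into the HITSystem 2.0 will be the first PMTCT appointment", and "the study will not directly target PMTCT uptake".
- **Duration of Retention.** Weeks retained are found "by subtracting the last date of documented service engagement from the date of enrollment". The article adds: "This will allow comparisons between total time retained in PMTCT services between groups". Statistical Analyses then specifies Kaplan-Meier curves that account for each woman's "eligible period of engagement (based on the timing of enrollment and accounting for premature infant or maternal mortality", followed by Cox regression if its assumptions hold.

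**The concern.** A woman who enters care late has fewer visits available to her. The article says so, then chooses two measures that keep this dependence and two tests that cannot take a covariate. Each arm is a single hospital, so randomization does nothing to balance entry timing. The sites already differ on the figures given under Study Sites (monthly EID volume 10 versus 18, infant transmission 2.7% versus 4.2%), and phone access is an entry condition only at the intervention site. If women at one hospital present earlier, that hospital will show more visits and more women with 4 or more, with no effect of the system.

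Gestational week at the first appointment cannot be changed by a system that starts at that appointment. Testing it in the same sentence as outcome comparisons, and listing entry by 14 weeks under Secondary Outcomes, invites a baseline difference to be reported as a result.

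**Working it through.** **1. The plan's own figure.** The article gives no power or sample size for these secondary measures. Its only figure is for the primary outcome: 47% versus 20%, two-sided alpha .05, 80% power, 54 per site. The pooled-variance formula gives (1.960·√(2·0.335·0.665) + 0.842·√(0.47·0.53 + 0.20·0.80))² / 0.27² = 46.8, so 47 per arm. With continuity correction this becomes 54 per arm, 108 in total. The figure reproduces, and nothing below alters it.

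**2. The ceiling on visits.** Assumptions, not in the article: birth at 40 weeks, one visit at entry and one every 4 weeks after. Maximum visits for entry at week g = 1 + floor((40 − g)/4).

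- g = 14: 1 + 6 = 7
- g = 28: 1 + 3 = 4
- g = 32: 1 + 2 = 3
- g = 36: 1 + 1 = 2

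On this schedule a woman entering after week 28 who attends everything still fails the 4-visit threshold. Another interval moves the cut-off but not the dependence.

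**3. Size of the false signal in visit count.** Further assumptions: entry normal around 22 weeks with SD 6, truncated to 5–38 weeks; PCR at 6 weeks; women who drop out leave uniformly over their eligible window; the same retention at both sites; 54 per site; Mann-Whitney at 5%; 1,000 simulated trials per cell. Rejection rates:

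| Retained to PCR | No entry difference | 2 weeks | 4 weeks |
|---|---|---|---|
| 47% | 4.7% | 17.3% | 53.0% |
| 68% | 5.6% | 22.7% | 67.3% |
| 80% | 5.4% | 28.5% | 78.0% |
| 90% | 4.5% | 30.2% | 83.4% |

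Monte Carlo error is at most √(0.5·0.5/1000) = 1.6 points. The 4-or-more threshold was not simulated separately. It is a cut of the same count, so the bias has the same direction.

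**4. Entry timing as an outcome.** Set side by side: exposure begins at the first PMTCT appointment (Intervention Specifications); uptake is not directly targeted (Discussion); gestational age is a covariate (Statistical Analyses, first paragraph). Yet gestational week at that appointment is tested among the between-site outcome comparisons, and entry by 14 weeks is a secondary outcome. Among enrolled women both are settled before the system can act.

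**5. Duration.** As worded, duration = enrollment date − last engagement date, which is zero or negative for every woman. In the right order, a fully retained woman scores (40 + 6) − g weeks: 32 if g = 14, 18 if g = 28, 10 if g = 36. Raw total time therefore also has a ceiling set by entry. Under the step 3 assumptions at 68% retained, a 2-week entry difference gives a mean duration difference of 1.7 weeks and 17% rejection by Mann-Whitney; a 4-week difference gives 3.3 weeks and 57%.

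**6. Does entry timing dominate?** Share of variance (r²) at the article's own retention levels, with entry SD 5 / SD 7:

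| Retained | Duration: entry age | Duration: fraction retained | Visits: entry age | Visits: fraction retained |
|---|---|---|---|---|
| 20% | 0.12 / 0.20 | 0.84 / 0.74 | 0.20 / 0.31 | 0.67 / 0.54 |
| 47% | 0.17 / 0.28 | 0.79 / 0.67 | 0.29 / 0.43 | 0.58 / 0.44 |
| 68% | 0.26 / 0.40 | 0.70 / 0.56 | 0.43 / 0.57 | 0.47 / 0.33 |

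At these levels duration reflects staying more than entry. For visit count the order reverses only at 68% with widely spread entry.

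**The case against.** The best defence is that the article already handles entry timing where it matters most. The duration analysis accounts for the eligible period, models control for gestational age, and attendance is also measured against each woman's own schedule. This stands for duration. No Mann-Whitney or chi-square test is named for it, so all that remains is the general sentence about comparing total time between groups. It does not rescue visit number and 4 or more: the tests named for those take no covariate.

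Second, comparing gestational age between sites is a sensible check, because covariates that differ are to be adjusted for. That is right, and the article claims no treatment effect on it. The fault is one of placement and labelling.

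Third, the reversed subtraction is a slip with plain intent. Agreed: no stated number depends on it.

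A reader might infer more, and the article does not support it:

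- *That duration and visit counts mostly measure entry timing.* Step 6 shows otherwise for duration at 20% to 68% retained, and for most of the visit-count cells.
- *That the Kaplan-Meier curves cannot show loss before, during and after delivery.* The article does not fix the time axis, and a condensed article may leave that to the analysis plan.
- *That early entry also flatters the measure of attending every scheduled visit.* With more visits due, attending all of them becomes harder, so the bias would run the other way.

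**Conclusion.** The point holds for the two visit-count measures and for the status of entry timing. With one hospital per arm, an entry difference of 2 weeks would raise the false-positive rate for visit count from about 5% to between 17% and 30%, and one of 4 weeks to between 53% and 83%, over 47% to 90% retained. These sizes rest on assumed entry distribution, visit interval and dropout pattern. The article gives no entry timing by site, so whether such a difference exists is unknown; with none, the tests keep their level.

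The duration part reduces to a wording correction and a limit on how total time is compared. These are secondary outcomes of a pilot, and the primary outcome definition and the 54 per site are untouched.

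**What to change.** 1. Analyse visits attended relative to visits due given gestational age at entry, or model visit count and 4 or more by regression with gestational age at entry as a covariate. Show raw medians and percentages as description only.
2. Move gestational week at first appointment and entry by 14 weeks to the baseline table, and use them only as covariates.
3. Define duration as last documented engagement minus enrollment date, in weeks.
4. Compare total time retained between groups only through the planned survival analysis that accounts for the eligible period.

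The >14-day rule for a missing visit should not be turned into the dropout event: a woman who is 15 days late and then returns would count as lost, which would create a new outcome.

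The cost is a little more analysis work and a few changed sentences. Gestational age at entry and scheduled dates are already needed for the planned measures, so no new data are required. Adjustment removes only the entry-timing part of a site difference; other differences between two single hospitals remain.
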